### BMI condition

#### **
*HaLT-Hamburg brief intervention*
**

The BMI is based on the German prevention program “*HaLT-Hart am Limit*” (“*Stop – close to the limit*”) and was adapted in a participatory process with cooperating practice partners, a youth-specific substance use counseling agency and an outpatient clinic for adolescents and young adults with substance use disorders. It is based on MI [28] and components reflect BMI elements as put forward by Spirito et al. [38]. The intervention is manual-based and consists of one 45-minute session. It’s 5 components are: 1. Introduction to the session with positive feedback on patient’s willingness to engage in the intervention, expression of interest and concern transporting a positive and empathic therapeutic mindset and explanation of the intervention’s aim and content. 2. A semi-structured interview assessing circumstances of the intoxication and alcohol-related risk behaviors. 3. Exploration phase incorporating discussion of motivation to drink, normative feedback, exploring pros and cons of current alcohol use, optional use of MI tools (i.e., importance and confidence ruler, decisional balance sheet) and establishment of future scenarios with changed/unchanged alcohol use. 4. Summary in which the facilitator structures and sums up what has been discussed, highlights personal responsibility for change and asks the patient for his/her conclusion from what has been discussed so far. 5. Closure of the session beginning with identification of drinking goals and potential barriers and development of strategies for goal attainment. The session is finished with a written agreement on drinking goals, the introduction of the cooperating youth-specific counseling agency and promotion of patient’s self-efficacy.

#### **
*Counseling session for caregivers*
**

Parents maintain significant influence on adolescent’s alcohol use and parental integration has been proposed to greatly enhance efficacy of targeted prevention programs [63]. When caregivers pick up the adolescent in hospital they can easily be reached and are offered a brief consultation by the same facilitator who delivered the BMI to the adolescent. Caregivers are encouraged to reflect on the AAI episode of the minor and develop strategies to prevent future risky alcohol use. They are provided with general information on alcohol and alcohol-related risks and are encouraged to seek further family- and/or substance use related services if required. Afterwards parents, facilitator and adolescent get together for a summary statement that focuses on supporting the adolescent’s sense of self-efficacy with regards to the attainment of his/her alcohol-related goals.

#### **
*Telephone booster*
**

Adolescents are contacted by telephone 6 weeks after discharge from hospital. The booster session is structured (manual-guided), lasts about 5–10 minutes and aims at enhancing content of the BMI and increasing motivation to pursue alcohol-related goals as set in hospital.

### Control condition

Participants in the control group are approached by a research assistant. After informed consent is given, they receive TAU which presently consists of oral and written information on cooperating youth- and family-orientated counseling agencies combined with the recommendation to contact a counseling agency and a flash drive with information on negative consequences of alcohol misuse for children and adolescents. Personal contact for TAU has a duration of 5–10 minutes.

### Treatment fidelity

Generally, the intervention is designed in a standardized way, yet it leaves facilitators with a certain leeway. This mentality reflects practitioners needs for flexibility and empathic focus on the client’s concerns in a MI spirit while keeping structure and content of the intervention sufficiently standardized [64]. Treatment fidelity is maintained using several strategies. First, the intervention (as the counseling session with parents/caregivers) is manualized. It provides clear guidelines and steps to be followed when carrying through the BI. Guidance is further enhanced by a short “memo-card”, which includes cues for core elements of the introduction, interview, exploration, summary and closure to the session and a reminder of the optional use of MI-tools. Additionally we developed a guide for delivering the telephone-booster. Second, all facilitators have a masters degree in psychology, social education work or related fields and are experienced in working with minors and their parents. Third, facilitators are initially trained by experienced and certified trainers (a clinical psychologist, a social educational worker and a research psychologist) in MI skills and in delivering the manualized BMI (12 hrs of training). On a bi-monthly basis facilitators are clinically supervised to discuss problems and experiences of implementation, engange in role-plays and receive retraining if required. Moreover, the manual was developed in a participatory approach by a team of experienced professionals including social education workers and senior clinical psychologists to raise practitioners acceptance and secure practicability under clinical conditions.

### Measures

Primary outcomes of the trial are reductions of past-month binge-drinking frequency, past-month quantity of alcohol consumption on a typical drinking day and alcohol-related problems in the past 3 months. We define binge drinking as consumption of 5 (4 for girls) or more alcoholic drinks at one occasion [59] and consider it as adequate primary outcome because it increases the risk for and often precedes AAI [4]. To assess binge drinking frequency we use a single question that is adapted from the Alcohol Use Disorder Identification Test Consumption subscale (AUDIT-C) [65] as used in a previous study [66]. Additional primary drinking outcome will be quantity of alcohol consumed on a typical drinking day as another indicator of risk for repeated AAI. For both alcohol measures (binge drinking and quantity of alcohol intake on a typical drinking day), we consider one unit of alcohol (standard drink) to include 10 g ethanol and we use a graphical overview of various types of drinks to help respondents answer the question and to ensure standardized responses. To assess alcohol-related behavioral problems we use the Rutgers Alcohol Problems Index (RAPI) [67] which is widely used and valid for an adolescent target population [68-71]. The secondary outcome concerns further seeking of counseling for alcohol use, which is retrospectively assessed by a single dichotomous (yes/no) question at both follow-ups and details on access and duration of services used.

Additionally we assess concurrent substance use following the assessment standards III of the German Society for Addicition Research and Therapy [72], repeated hospitalization due to AAI, general psychopathology through a short version of the Symptom Checklist SCL-9-K [73] and the Screening of Psychological Disorders in Adolescence (SPS-J) [74] as a behavioral screening instrument for early detection of externalizing and internalizing problems. Furthermore we assess readiness to change through an algorithm [75] allowing allocation of individuals to the different stages of change as proposed by Prochaska and DiClemente [76] and alcohol-related cognitive variables such as knowledge (modified from [77], social norms [77], self-efficacy (selected items of the Alcohol Abstinence Self Efficacy Scale (AASE-G) [78]) and attitudes through a 9-item semantic differential [79]. All assessment instruments are based on self-reports. We collect basic demographic data on age, gender, ethnic- and socioeconomic family status.

### Additional components of evaluation

As mentioned above we include additional components to evaluate effectiveness alongside our RCT design. In summary, we examine quantitative and qualitative process data on intervention delivery, implementation and receipt from intervention providers, receivers and regular ED staff which is guided by the framework of RE-AIM (Reach, Effectiveness, Adoption, Implementation, and Maintenance) as suggested by Glasgow and colleagues [80]. This framework represents a systematic approach to the evaluation of research translation potentials into practice and has been applied for the evaluation of implementation of BI’s in ED before [34].

#### **
*Intervention implementation and delivery*
**

We will explore qualitative contextual information about AAI treatment in the participating clinics and whether the *HaLT-Hamburg* intervention is familiar to the clinic staff. Furthermore we examine attitudes, level of interest/commitment and perceived barriers for routine implementation among ED staff (medicals, nurses) and BMI facilitators. This information includes structural conditions affecting delivery (e.g., is the BMI delivered in a seperate room or a corridor with hospital staff, patients and visitors passing by) as well as duration of session and type and duration of possible interruptions. Facilitators complete a short record indicating details about intervention delivery (such as content, MI-techniques used, referral to further counseling) after each BI. Finally, heads of departments will be interrogated providing information on perceived barriers and ressources for long term project implementation.

#### **
*Receipt and acceptance of BMI*
**

Patient’s acceptance of the intervention is evaluated with the Treatment Satisfaction Questionnaire (Fragebogen zur Patientenzufriedenheit ZUF-8, [81]) using 8 items (e.g. “To what extend did the counselling session meet your needs?”). For adherence to MI spirit patients rate their perception of facilitator’s therapeutic skills with 8 items (e.g. “the facilitator respects me”, “the facilitator seems empathic”) on a 4-point response scale immediately after the BI session in hospital (Index of Basic Therapeutic Skills (BIS) (short version) [82].

#### **
*Feasibility*
**

Similar to the approach of Linakis et al. [23] we assess feasibility through the number of enrolled participants and the number of those who complete all elements of the intervention. An indication for feasibility will be given if at least 80% eligibles participate and 90% or more of those who participate complete the intervention before discharge from hospital.

### Randomization

Because of limited resource availability, individual level random assignment of eligible participants to BMI or control condition is not feasible in this study. Instead a stratified cluster randomization is deemed appropriate with weekends (N = 129) as stratum and hospital (N = 6) on a weekend as unit of randomization. Over a data collection period of 30 months this yields a total of N = 774 possible clusters. This approach leads to a high number of clusters, which is highly recommended [83] and assures that at each weekend patients in one half of the hospitals are assigned to the BMI and the other half to the control condition. The total amount of possible combinations between strata and hospitals is balanced in a way that each clinic acts equally often as control and BMI condition and assures that all clinics are either control or BMI condition at each weekend. The resulting randomization plan was established prior to the data collection process by a research assistant from the Department of Medical Biometry and Epidemiology (University Hospital Hamburg-Eppendorf) who is not involved in the project, using the statistical software package SAS, Version 9.3 [84].

### Sample size

The sample size is calculated for the three primary outcomes binge-drinking frequency, quantity of alcohol consumption on a typical drinking day and alcohol related problems at 3 month follow-up. Type I error is set to 5% for each of these outcomes. With an effect size of 0.26 and a power of 80%, 2 × 153 patients need to be included if randomization occurs at patient level. With an assumed intra-cluster correlation of 0.05 and an average of 1.264 included patients per cluster, we calculated a design effect of 1.013. Hence, the required sample size increases to 156 patients and 154 clusters per group, resulting in a total sample of N = 312. Clusters (hospitals per weekend) without patients will not be included in the analysis. With an expected participation rate of 80%, we anticipate N = 390 ED patients to be assessed for eligibility over a recruitment period of 30 months in the six participating hospitals. Based on a prior pilot-study [4], this sample size is feasible.

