
### Objectives and hypotheses

The objective of this study is to evaluate the effectiveness of a manual-based BMI for adolescents admitted for AAI in the ED. Effectiveness will be evaluated by expected reductions of binge-drinking frequency (5 or more standard drinks at one occasion (4 for female) [59]), quantity of alcohol consumption on a typical drinking day and alcohol related problems at 3 and 6 month follow-up. Our primary hypothesis is that children and adolescents under the age of 18 years who receive the manualized BMI following AAI hospitalization will show lower levels on these outcomes when compared to controls not receiveing this treatment. We also include further health care utilization in response to the BMI as secondary outcome. Help seeking in the care system as recommended in our BMI is closely related to intention to change [60] and appropriate for additionally judging intervention effectiveness. We thus hypothesize that children and adolescents who receive the BMI will significantly more often access further counseling regarding alcohol use in the 6 months following hospitalization than children and adolescents who do not receive the BMI. Moreover, we will examine a number of expected moderating variables such as psychopathological symptoms, drinking history, concurrent substance use and family environment. Finally, alongside our RCT we include additional evaluation components that focus on process, context and practical implications for BMI delivery under “routine conditions” in the ED setting.

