### Statistical analysis

Basic descriptive statistics will be calculated for baseline variables, and according to trial arm (BMI vs. control). Intention-to-treat (ITT) analysis will be based on available data from all randomized patients at 3 and 6 month follow-up. In case of missing follow-up values multiple imputation will be performed [85]. For primary and secondary hypotheses we will use linear mixed models adjusted for baseline differences to examine differences between intervention and control group with intervention condition as fixed effect and clusters (hospital on a weekend) as random effect. The two-sided ?-level is set to 0.05. Additional analysis will be conducted on a per-protocol analysis set. Process data on intervention delivery, implementation and receipt will be analyzed in subsequent steps.

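### Three primary outcomes each get a full 5% under one primary hypothesis, with no stated success rule and two different accounts of the time point, so the overall conclusion of effectiveness is not protected

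*Protocol article*

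**What the plan says.** The Measures section lists three primary outcomes: "Primary outcomes of the trial are reductions of past-month binge-drinking frequency, past-month quantity of alcohol consumption on a typical drinking day and alcohol-related problems". It does not rank them for testing, although it introduces binge drinking first, with a justification, and then presents typical-day quantity as an additional primary drinking outcome.

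Objectives and hypotheses gathers the three under one primary hypothesis: adolescents who receive the intervention "will show lower levels on these outcomes when compared to controls". It says that effectiveness will be judged on binge-drinking frequency, "quantity of alcohol consumption on a typical drinking day and alcohol related problems at 3 and 6 month follow-up".

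The Sample size section uses the same three outcomes but one visit: "quantity of alcohol consumption on a typical drinking day and alcohol related problems at 3 month follow-up". It then allots the error: "Type I error is set to 5% for each of these outcomes". The size itself is given as "With an effect size of 0.26 and a power of 80%, 2 × 153 patients need to be included if randomization occurs at patient level", raised to 156 per group (N = 312) for clustering.

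Statistical analysis sets a two-sided level of 0.05 and bases the intention-to-treat analysis on data from both follow-ups. The article does not say whether one significant outcome is enough or all three are needed.

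**The concern.** The trial is built to deliver one answer. Implications for practice says there is a clear perspective of further funding if the intervention proves effective. With three outcomes, each tested at the full 5%, that answer depends on a rule the article does not give.

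Under an any-outcome rule, the chance of a false positive conclusion exceeds that of a single 5% test. Under an all-outcomes rule, error is controlled, but the chance of success is below the 80% used to size the trial. The time point adds a second ambiguity, because the hypothesis refers to two visits and the sample size to one. Unless the rule is fixed in advance, which outcome and which visit count as success can be decided after the results are known.

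**Working it through.** **Inputs from the protocol article.** Three primary outcomes (Measures); 3 and 6 months (Objectives and hypotheses); 3 months only, 5% per outcome, effect size 0.26, 80% power, 153 per arm before clustering (Sample size); two-sided 0.05 (Statistical analysis).

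**Assumed, because not given.** A common correlation between the three test statistics of 0 to 0.8; a correlation of 0.5 between visits for the six-test illustration; test statistics approximately normal.

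**Step 1: the plan's own figure.** For a two-sided comparison of two means with a standardised difference of 0.26, n per arm = 2 × (1.960 + 0.842)² / 0.26² = 232.2, so 233. The stated 153 is not reproduced, and 153 per arm gives about 62% power. An unstated baseline adjustment (a correlation of about 0.58) would recover 153. This is a separate matter. The steps below take 80% per outcome at face value.

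**Step 2: any of three at 3 months, no true effect.**
- Two-sided family-wise error if independent: 1 − 0.95³ = 0.143.
- False benefit only (significant in the hypothesised direction, 2.5% per test) if independent: 1 − 0.975³ = 0.073.

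**Step 3: all three required.** With 80% each and independence, joint power = 0.80³ = 0.512. Error stays at or below 5%.

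**Step 4: correlated outcomes.** Multivariate-normal simulation, 1 million draws per row; for power, each statistic has mean 1.960 + 0.842 = 2.802.

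| Outcome correlation | Any of three, two-sided error | Any of three, false benefit | All three, joint power |
|---|---|---|---|
| 0 | 14.3% | 7.4% | 51% |
| 0.3 | 13.6% | 6.8% | 57% |
| 0.5 | 12.6% | 6.3% | 61% |
| 0.7 | 11.0% | 5.5% | 66% |
| 0.8 | 9.8% | 4.9% | 69% |

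The simulated 7.4% in the first row agrees with the exact 7.3% within simulation error.

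**Step 5: if success at either visit also counted.** With a visit correlation of 0.5, the two-sided error over six tests is about 25% (outcome correlation 0) to 17% (0.8), and false benefit about 13% to 9%. This is an illustration only, since the article does not say that success at either visit is enough.

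**Step 6: cost of an equal split of alpha.** At 0.05/3 the two-sided critical value is 2.394. Power for an outcome planned at 80% is Φ(2.802 − 2.394) = 0.658.

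**The case against.** The strongest reply is that the plan promises only what it states: 5% for each outcome, and a sample size calculated for each. It claims neither family-wise control nor joint power. That stands. A reader might infer that no reading of the plan can satisfy both 5% and 80%, or that these figures are wrong because there are three outcomes. The document does not support that, because read per outcome both are as stated. The gap concerns the single primary hypothesis and the conclusion drawn from it.

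A reader might also infer six primary tests and quote 1 − 0.95⁶ = 26.5%. That is a worst case. The article never says that success at either visit suffices, nor that separate tests are run at each visit, and independence is implausible for related drinking measures in the same patients.

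The hypothesis is directional, and the two-sided family-wise rates also count significant harm. The risk of wrongly declaring benefit is about half as large. That correction stands, and both columns are shown.

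Finally, multiplicity procedures are often left to an analysis plan that is not shown here. Silence alone would therefore be no finding. But the article is not silent: it assigns a full 5% to each primary outcome. A later plan that split alpha would depart from that statement and from the sample size built on it.

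**Conclusion.** The point holds in a limited form and should be fixed. The per-outcome figures are as stated, but the overall conclusion of effectiveness is unprotected because the success rule is open and the hypothesis and the sample size differ on the time point. At 3 months, with assumed outcome correlations of 0 to 0.8:

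- an any-of-three rule has a two-sided family-wise error of about 14% to 10%, or about 7% to 5% for false benefit against 2.5% for one test;
- an all-three rule has joint power of about 51% to 69%, conditional on the stated 80% per outcome.

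Counting success at 6 months as well would raise the error further, by an amount that depends on a rule and on correlations the article does not give.

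**What to change.** Before any outcome analysis, state in the protocol and the analysis plan that:

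1. 3 months is the primary time point, as in the sample size, and 6 months is secondary;
2. the three outcomes are tested in fixed order, each at two-sided 5%: binge-drinking frequency, then typical-day quantity, then alcohol-related problems, stopping at the first non-significant result.

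The order follows the article's own listing and its description of quantity as an additional drinking outcome; the article does not itself set a testing hierarchy, so the investigators must agree to it.

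**Cost.** A short addition to the text and no further patients. The first outcome keeps its full 5% and its planned power. The downside is that later outcomes can be claimed only if the earlier ones succeed. At 80% each, the chance of claiming the second is 0.80² = 64% if independent, and the chance of claiming all three is the 51% to 69% shown above.

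**Alternative.** If no order can be agreed, Holm's procedure across the three outcomes at 3 months also controls the family-wise error. Power at its first step falls from 80% to about 66% per outcome.

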**Methods:**

The trial design is a parallel two-arm cluster randomized-controlled trial with follow-up assessment after 3 and 6 months. N = 312 participants aged 17 years and younger will be recruited Fridays to Sundays in 6 pediatric clinics over a period of 30 months. Intervention condition is a manual-based brief motivational intervention with a telephone booster after 6 weeks and a manual-guided intervention for caregivers which will be compared to treatment as usual. Primary outcomes are reduction in binge drinking episodes, quantity of alcohol use on a typical drinking day and alcohol-related problems. Secondary outcome is further treatment seeking. Linear mixed models adjusted for baseline differences will be conducted according to intention-to-treat (ITT) and completers (per-protocol) principles to examine intervention effects. We also examine quantitative and qualitative process data on feasibility, intervention delivery, implementation and receipt from intervention providers, receivers and regular emergency department staff.

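### The printed inputs (effect size 0.26, 80% power, two-sided 5%) need about 233 patients per arm, not 153; on those inputs the trial has about 62% power.

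*Protocol article*

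**What the plan says.** The Sample size section covers three primary outcomes at the 3-month follow-up: binge-drinking frequency, quantity on a typical drinking day, and alcohol-related problems. It says "Type I error is set to 5% for each of these outcomes", so there is no split of alpha across outcomes. It then states "With an effect size of 0.26 and a power of 80%, 2 × 153 patients need to be included" for the case of individual randomisation. Clustering is added next: "With an assumed intra-cluster correlation of 0.05 and an average of 1.264 included patients per cluster, we calculated a design effect of 1.013". This raises the size to 156 per group and 312 in total. An 80% participation rate turns 312 into 390 patients to be assessed.

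The sidedness is given in the Statistical analysis section, where testing is two-sided and the "level is set to 0.05". The Randomization section gives 1:1 allocation, because each weekend "patients in one half of the hospitals are assigned to the BMI and the other half to the control condition". The Abstract repeats the total: "N = 312 participants aged 17 years and younger will be recruited Fridays to Sundays".

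The article does not say how the effect size of 0.26 is standardised. It gives no standard deviation, no correlation between baseline and follow-up, and no variance reduction for the sample size.

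**The concern.** The article prints every input that a two-group comparison of means needs, and then a result that does not follow from them. The gap is 153 against 233 per arm, about one third of the requirement, so rounding cannot explain it.

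The step from 0.26 to 153 carries the rest of the plan: 156 per arm, N = 312 and 390 assessed. If the inputs are right and the result is wrong, the trial is well short of 80% power for the effect it says it targets, on each primary outcome. A non-significant result would then be weaker evidence against the intervention than a reader relying on the stated 80% would think. This matters in practice: the article says that variants of the programme run at more than 160 locations, and it ties further funding to the intervention proving effective.

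**Working it through.** **Inputs.** Effect size d = 0.26, power 80%, type I error 5% per outcome, ICC 0.05 and 1.264 patients per cluster (all Sample size); two-sided testing (Statistical analysis); 1:1 allocation (Randomization).

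**Step 1: reproduce 153.** Patients per arm, individually randomised:

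n = 2 × (z₀.₉₇₅ + z₀.₈₀)² / d² = 2 × (1.960 + 0.842)² / 0.26² = 232.2, so 233.

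The two-sample t-test gives 233.2, so 234. The printed 153 is not reproduced.

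**Step 2: reproduce the next step.** Design effect = 1 + (1.264 − 1) × 0.05 = 1.0132. Then 153 × 1.0132 = 155.02, rounded up to 156; 2 × 156 = 312; 312 / 0.80 = 390. All of these agree with the article, so the fault lies only in the step from 0.26 to 153.

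**Step 3: other readings of the inputs.**

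| Reading | Patients needed |
|---|---|
| One-sided 5% | 183 per arm (t-test 184) |
| One-sided 10% | 134 per arm |
| Two-sided, Bonferroni 0.05/3 | 310 per arm |
| Wilcoxon, relative efficiency 0.955 | about 244 per arm |
| Change score, correlation 0.5 | 233 per arm |
| 0.26 read as Cohen's f | about 118 in total |
| 0.26 read as a correlation | about 114 in total |
| One-sample or paired test | 117 |

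None is within 3% of 153 per arm (306 in total).

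**Step 4: what 153 does correspond to.** Solving for d at n = 153 and 80% power gives 0.32 two-sided, or 0.285 one-sided.

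**Step 5: power at d = 0.26.**

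- 153 per arm: 62% two-sided (normal 62.3%, t-test 62.1%); 73 to 74% one-sided.
- 156 per arm after the design effect, an effective 156 / 1.0132 = 154 per arm: 62 to 63% two-sided (normal 62.6%, t-test 62.3%).

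**Step 6: total needed for 0.26 with the article's design effect.** Unrounded, 2 × 232.2 × 1.0132 = 471. Rounding up at each step, as the article does, 233 × 1.0132 = 236.1, so 237 per arm and 474 in total. Starting from the t-test, 234 × 1.0132 = 237.1, so 238 per arm and 476 in total. The plan has 312.

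**Step 7: the correlation that would rescue 153.** If 0.26 is scaled to the unadjusted standard deviation and the model adjusts for the baseline value, n = 232.2 × (1 − r²). Setting n = 153 gives r² = 1 − 153 / 232.2 = 0.341, so r = 0.58. For comparison, r = 0.5 gives 175 per arm and r = 0.6 gives 149.

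**The case against.** The strongest reply is that 62% is the power of an analysis the trial does not plan. The Statistical analysis section already adjusts the mixed models for baseline differences. If 0.26 is scaled to the unadjusted standard deviation, power at 156 per arm (design effect 1.0132, normal approximation) rises with the baseline-to-follow-up correlation: 67% at 0.3, 70% at 0.4, 75% at 0.5, 80% at 0.58 and 81% at 0.6. On this view 62% is the lower end of a range, and 153 may be a correct number with an unreported assumption behind it.

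Other unstated routes also land near 153. Averaging two follow-ups that correlate at about 0.32 gives 153. Averaging three measurements that correlate at 0.5 gives 232.2 × (1 + 2 × 0.5) / 3 = 154.8. A joint test of all three outcomes with pairwise correlation 0.2 reaches 80% power at 153 per arm. A journal article may also leave such details to a fuller protocol.

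Part of this stands. An arithmetic slip cannot be told apart from an undisclosed assumption, and actual power could exceed 62% if baseline adjustment removes variance. It does not clear the text:

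- The sentence presents its inputs and result as complete, and they disagree. That is an incorrect statement, not an omitted detail.
- The averaging routes do not fit a calculation made for 3 months, and the joint test does not fit a 5% level set for each outcome.
- The baseline route would need a correlation of about 0.58 on all three primary outcomes. If 0.26 is already an adjusted effect, there is no gain left and 233 per arm applies.

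**Conclusion.** The concern holds. On the printed inputs the requirement is 233 per arm (234 by the t-test) before clustering, not 153. The planned 156 per arm gives about 62% power at 0.26, and 80% power is reached only at an effect size of about 0.32. The chance of missing the targeted effect is about 38%, nearly twice the stated 20%.

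The 62% rests on three assumptions: 0.26 is a standardised mean difference, the sizing takes no credit for baseline adjustment, and every patient has a 3-month outcome. The second is where the figure could improve, by the amounts given above for each correlation. The third is favourable to the trial: the Sample size section makes no allowance for loss to follow-up, since its 80% is a participation rate.

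Because this is the power claim for all the primary outcomes, it must be corrected.

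**What to change.** Keep N = 312 and correct the Sample size section in one of two ways:

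1. **If no variance reduction was assumed:** state that 156 patients per arm, with a design effect of 1.013 and a two-sided 5% level per outcome, gives 80% power for a standardised difference of 0.32 and about 62% for 0.26.
2. **If baseline adjustment was assumed:** define the effect size (which standard deviation scales it), state the baseline-to-follow-up correlation that was used, which would have to be about 0.58, and give its source. The Statistical analysis section already mentions adjustment for baseline differences; make it explicit that each primary outcome is adjusted for its own baseline value. A value of 0.58 should be given only if it was really an input, not worked back from 153.

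In both cases, state the sidedness beside the calculation. The cost is wording only, with no added patients. Under the first option, the stated power or detectable effect becomes less favourable.

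### In the visible text N = 312 is both the number required at 3 months and the number recruited, so the stated 80% power presupposes essentially complete 3-month follow-up

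*Protocol article*

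**What the plan says.** The Sample size section of the protocol article powers the trial for the three primary outcomes at the 3-month follow-up. Its inputs are:

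- Error rate: "Type I error is set to 5% for each of these outcomes". The Statistical analysis section makes the test two-sided.
- Effect and power: "With an effect size of 0.26 and a power of 80" per cent.
- Size before clustering: "2 × 153 patients need to be included if randomization occurs at patient level".
- Clustering: "With an assumed intra-cluster correlation of 0.05 and an average of 1.264 included patients per cluster, we calculated a design effect of 1.013". This gives 156 patients and 154 clusters per group, 312 patients in total.
- Recruitment: "With an expected participation rate of 80%, we anticipate N = 390 ED patients to be assessed for eligibility".

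The Abstract (Methods) uses the same total for enrolment: "N = 312 participants aged 17 years and younger will be recruited". The Feasibility section also uses 80% for the share of eligible patients who take part, so the rate describes entry to the trial and not retention in it.

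Follow-up is by telephone at 3 and 6 months (Recruitment and procedure). On incomplete data the Statistical analysis section says: "In case of missing follow-up values multiple imputation will be performed". No loss rate or attrition inflation appears in the visible text. Figure 1, captioned as a flow diagram with anticipated case numbers, is not shown.

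**The concern.** A sample size calculated for an outcome at 3 months is a number of patients with that outcome. When the same number is set as the enrolment target, the stated power assumes that practically every enrolled adolescent is reached by telephone at 3 months. The plan provides for missing values in the analysis but, as far as the text shows, not in the sample size.

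What is at stake is how the result will be read. If some participants are lost, a null finding set against a stated power of 80% would look like stronger evidence of no effect than the data can give.

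**Working it through.** **1. The plan's chain from 153 to 390.**

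- Design effect: 1 + (1.264 − 1) × 0.05 = 1.0132. This agrees with the stated 1.013.
- 153 × 1.0132 = 155.02, rounded up to 156 per arm, 312 in total. This agrees.
- 312 / 0.80 = 390, and 390 × 0.80 = 312 exactly. The participation rate uses up the whole difference between 390 and 312, so nothing remains for loss after enrolment.

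**2. The starting figure of 153.** For two means with a standardised effect d, two-sided 5% and 80% power, n per arm = 2 × (1.960 + 0.842)² / d². With d = 0.26 this gives 233, not 153. A one-sided test would give 183. Power at 153 per arm and d = 0.26 is 62.3%. The effect that 153 per arm supports with 80% power is √(2/153) × 2.802 = 0.320. A baseline correlation of about 0.58, used in an adjusted analysis, would reconcile 153 with 0.26, since √(1 − 153/232.2) = 0.584. The article states no such correlation.

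This is a separate matter. To isolate the effect of attrition, step 3 accepts 153 per arm as giving 80% power and uses d = 0.320.

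**3. Effect of loss to follow-up.** The document gives no loss rate, so 5% to 30% is an assumed range. Effective n per arm = 156 × (1 − loss) / 1.0132. Power = Φ(0.320 × √(n/2) − 1.960). Detectable effect at 80% power = 2.802 × √(2/n).

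| Assumed loss | Analysed (total) | Effective n per arm | Power for 0.32 | Detectable effect |
|---|---|---|---|---|
| 0% | 312 | 154.0 | 80% | 0.32 |
| 5% | 296 | 146.3 | 78% | 0.33 |
| 10% | 281 | 138.6 | 76% | 0.34 |
| 20% | 250 | 123.2 | 71% | 0.36 |
| 30% | 218 | 107.8 | 65% | 0.38 |

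Letting the average cluster size shrink along with the loss changes power by less than one percentage point.

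**4. The same losses at the stated effect of 0.26.** With all 312 followed, power is 62.6%. With 5%, 10%, 20% and 30% loss it is 60%, 58%, 53% and 48%. Loss itself therefore accounts for about 2, 5, 9 and 15 points. The step from 80% to about 62% is present before anyone is lost.

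**5. The cluster figures.** 156 / 1.264 = 123 clusters per group, not the stated 154. Conversely, 2 × 154 × 1.264 = 389, close to 390. So the figures 154 and 1.264 fit 390 included patients better than 312.

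**The case against.** **The flow diagram is missing.** Anticipated numbers at 3 and 6 months would normally stand in Figure 1, and the article condenses a fuller protocol. This stands as a limit. One cannot say that the plan has no allowance, only that the visible text shows none. If Figure 1 does show fewer patients at 3 months, it would still need reconciling with text that gives 312 as both required and recruited.

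**The reserve may be there under another label.** On the cluster figures, 390 could be the number included and 312 the 80% of them analysed, which would be exactly an allowance for 20% loss. The wording is against this: the Abstract recruits 312, the Sample size section attaches 390 to patients assessed for eligibility, and the Feasibility section uses 80% for participation. But the numbers conflict, and only the sponsor can settle which was meant.

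**Imputation recovers something.** This is partly right. A missing 3-month value imputed from baseline and 6-month data need not cost a whole patient's information, so the powers in the table are approximate and lean low. No such gain is quantified in the article, and imputation does not in general restore the full information.

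**Expected loss is not established.** Providing for missing values is routine and implies no particular rate, and vouchers for completed follow-ups are a means of keeping participants. That also stands. At 5% loss the shortfall is only about 2 points.

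**A stronger reading to avoid.** A reader might infer that the missing attrition allowance is why the trial does not have 80% power, and might set the 58%, 53% and 48% found at an effect of 0.26 against the promised 80%. The document does not support this. It states no loss rate, and most of that gap is already there with complete follow-up.

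**Conclusion.** The point holds in a limited form. As the text stands, 312 is both the requirement and the enrolment target, and the 80% rate acts before enrolment. The stated power is therefore conditional on essentially complete 3-month follow-up.

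The cost of departing from that is small at 5% loss and material from about 20%, where power is some 9 points below 80% and the detectable effect is 0.36 instead of 0.32. These sizes rest on three assumptions: the loss rates, which are not the sponsor's; acceptance of 153 per arm as giving 80% power; and no information regained through imputation. The shortfall at the stated effect of 0.26 is a separate and larger fault and should not be charged to attrition.

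The point is worth acting on because it corrects a stated figure at little cost.

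**What to change.** Leave the recruitment target unchanged and amend the Sample size section as follows:

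- State the 3-month retention assumed.
- Restate power and detectable effect for the number expected to be analysed. For example, at an assumed 80% retention about 250 would be analysed (312 × 0.80), giving about 71% power for an effect of 0.32, or 80% power for an effect of 0.36.
- Reconcile 312 and 390 with 154 clusters per group and 1.264 patients per cluster, and say which number is assessed, which included and which analysed. Check that Figure 1 agrees.

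If 390 proves to be the number included and 312 the number analysed, the reserve exists. The correction is then to the labels in the Abstract and the Sample size section.

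The change is to wording only. It adds no patients and alters neither design nor analysis. Its price is a less favourable stated power.
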